### Statistical analysis

#### Descriptive statistics

Means, standard deviations and frequencies will be used to describe outcome, background and baseline variables.

#### Analysis effectiveness

The primary variable for effectiveness will be analyzed in a covariance model with the COPM scores after three months (T1) as dependent variable. The baseline COPM scores (T0) and the minimization factors will be covariates. Two-sided 95% confidence intervals will be calculated. The analysis follows the principle of intention to treat. Similarly, a secondary analysis will be done evaluating the secondary outcome variables and outcomes for six months. Regarding the caregiver outcomes, we plan a subanalysis for caregivers with low perceived burden at baseline (Zarit Burden Interview (ZBI) ≤20) and high perceived burden of care (ZBI >20).

#### Analysis cost-effectiveness

An economic evaluation will be done from a societal perspective by evaluating the differences in total costs in the control and experimental group at three and six months. Total costs include care consumption and productivity loss of patients and caregivers related to Parkinson’s and caregiver’s hours of care provision to the patient. The number of OT sessions and total time spent on OT, will be translated as direct costs of the intervention. Differences in costs between groups over a six-month timeframe will be estimated using regression analysis taking into account potential co-variants. Secondly, utility will be calculated as quality adjusted life year (QALY) over a timeframe of six months using the trapezium rule. QALYs for patients and caregivers are derived from the EuroQol EQ-5D scores using the EQ-5D health tariffs for the Dutch population [50]. Then, cost and QALY differences are combined in an incremental cost-effectiveness ratio (ICER), and using the bootstrap method, confidence intervals surrounding this ICER will be estimated. We also measure cost-effectiveness by costs per successful treatment. A successful treatment is a treatment with a clinical relevant positive change in the COPM (+ 2 points) at six months. Reporting the ICER as cost per successful treatment may provide decision-makers with a relatively intuitive means of assessing cost-effectiveness, because the denominator of the incremental ratio is calculated using a clinically meaningful objective.

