## Methods/Design

### Trial design

A multicenter, assessor-blinded, two-armed randomized controlled clinical trial will be conducted. Patients and their caregivers will be assigned to the experimental group or to the control group in a ratio of 2:1, respectively. This way the patients have twice as much chance to be in the intervention than in the control group. This ratio will enhance the inclusion, whereas there will hardly be any power loss compared to a 1:1 randomization. Randomization will be based on a computerized minimization algorithm with the following minimization factors: baseline primary outcome measure (Canadian Occupational Performance Measure (COPM) performance: <5; ≥5), severity of disease (Hoehn and Yahr (H&Y) score: <3; ≥3), gender and age group (<65 years; ≥65 years) of the patient, and patient receiving physiotherapy at baseline (yes/no).

Data on observational and self-reported outcome measures will be collected at baseline, after three months (post-intervention) and after six months (follow-up) (see Figure 1).

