### Intervention

The OTiP intervention protocol follows the principles and recommendations for diagnostics and interventions as described in the Dutch guidelines for OT in Parkinson’s disease [18,19]. The approach is client centered including shared decision making and supporting self-management of the patient and caregiver in dealing with problems in daily activities. The trial therapist receives the patient’s priorities in problems in daily functioning as evaluated at baseline with the COPM [25]. The baseline COPM priorities and additional information from the diagnostic phase shape the treatment plan. The intervention is delivered at the patient’s home for a period of ten weeks within three months. Depending on complexity of goals, the amount of sessions can vary with a maximum of ten sessions (only patient goals) or 16 sessions (patient and caregiver goals) of 45 to 60 minutes. Between the three and six month assessments, no OT will be received. An exception is when in incidental cases of lengthy procedures to apply for aids and adaptations, a follow-up contact after delivery is necessary to ensure safe and proper use of the equipment. Figure 2 summarizes the process and characteristics of the OTiP intervention.

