### Assessment procedures

Data from patients and caregivers will be collected at baseline (T0), three months (T1) and six months (T2) by three research assistants (see Table 1). Another eight selected and trained occupational therapists will score the Perceive Recall Plan Perform system (PRPP [26]) in an activity that is video recorded by the assessor. All assessors and PRPP-scorers are blinded for group allocation and each participant will be followed up by the same assessor. Patients and caregivers also fill in self-report questionnaires. Observational tests or measures that follow a semi-structured interview format are conducted in the patient’s home environment by the assessor. Considering possible response fluctuations in Parkinson’s, measures are administered within one to two hours after medication intake (the *on* phase). For budgetary reasons, the six month assessment is conducted by phone and therefore, does not include observational measures.

**Table 1 T1:** Outcome measures

**Participant**	**Outcome measure**	**Instrument**	**baseline**	**3 months**	**6 months**
**Patient**	Self-perceived performance in daily activities^a^	Canadian Occupational Performance Measure (COPM; performance rating) [25]	*√*	*√*	*√*
	Self-perceived satisfaction with performance in daily activities	Canadian Occupational Performance Measure (COPM; satisfaction rating) [25]	*√*	*√*	*√*
	Objective performance in daily activities	Perceive Recall Plan Perform system (PRPP) [26]	*√*	*√*	-
	Participation	Activity Card Sort (ACS) [27,28]	*√*	*√*	-
		Utrecht Scale for Evaluation of Rehabilitation Participation (USER-P; satisfaction part) [29,30]	*√*	*√*	*√*
	Health-related quality of life	Parkinson’s Disease Questionnaire (PDQ-39) [31-33]	*√*	*√*	*√*
	Impact of fatigue	Fatigue Severity Scale (FSS) [34,35]	*√*	*√*	*√*
	Mood	Becks Depression Inventory (BDI) [36]	*√*	*√*	*√*
**Caregiver**	Perceived caregiver burden	Zarit Burden Interview (ZBI) [37]	*√*	*√*	*√*
	Objective caregiver burden	Objective care burden questionnaire; hours of care	*√*	*√*	*√*
	Mood	Hospital Anxiety and Depression Scale (HADS) [38]	*√*	*√*	*√*
**Both**	Quality of life	Euroqol EQ-5 D [39]	*√*	-	*√*
	Quality of life overall	Visual Analogue Scale for Quality of life; VAS QoL	*√*	*√*	*√*
	Proactive coping	Utrecht Proactive Coping Competence scale (UPCC) [40]	*√*	*√*	*√*
	Resource utilization	Resource utilization questionnaire: patient and caregiver version	*√*	*√*	*√*

^a^Primary outcome measure.

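### EQ-5D is not collected at three months, so the six-month QALY is a straight line that ignores any utility difference at the end of treatment; the sign of the resulting error depends on a utility path the protocol does not give

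*Protocol article*

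**What the plan says.** Under Analysis cost-effectiveness, the article says that "utility will be calculated as quality adjusted life year (QALY) over a timeframe of six months using the trapezium rule". The utilities have one source: "QALYs for patients and caregivers are derived from the EuroQol EQ-5D scores". The QALY difference then goes into the ratio: "cost and QALY differences are combined in an incremental cost-effectiveness ratio (ICER".

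Table 1 (Assessment procedures) ticks EQ-5D, for patients and caregivers, at baseline and six months and puts a dash at three months. No other row has a dash there. COPM, PRPP, ACS, USER-P, PDQ-39, FSS, BDI, ZBI, objective care burden, HADS, VAS QoL, UPCC and resource use are all collected at three months.

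On timing, Trial design places the later assessments "after three months (post-intervention) and after six months (follow-up". Treatment is delivered "for a period of ten weeks within three months", and "Between the three and six month assessments, no OT will be received", apart from incidental follow-up contacts about aids and adaptations. The primary effectiveness analysis uses COPM performance at three months. The economic evaluation works by "evaluating the differences in total costs in the control and experimental group at three and six months".

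**The concern.** With EQ-5D at two times only, the trapezium rule is a single trapezium: each participant's utility is assumed to move in a straight line from baseline to six months. Three months is when treatment has just ended, when the primary effect is assessed, and after which almost no occupational therapy is given. If utility changes slope anywhere, that is a natural place for it, and the planned QALY cannot show it.

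Costs are treated differently. Resource use is recorded at three months, and the intervention cost, which falls almost entirely in the first three months, is counted in full. So the numerator of the cost-utility ratio has a three-month point and the denominator has none. Cost-effectiveness is one of the trial's stated aims, so the error matters, although it does not touch the clinical comparison.

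**Working it through.** The protocol states no utility, QALY or ICER figure, so there is no published number to reproduce. The inputs are the EQ-5D schedule (0 and 6 months, Table 1), the trapezium rule over half a year (Analysis cost-effectiveness) and the existing three-month assessment (Trial design). The utility differences between groups are assumptions, because the documents give none.

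**Formulas.** Let d3 and d6 be the differences in mean utility (intervention minus control) at three and six months, with zero difference at baseline.

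- Planned, two points: 0.5 × (0 + d6)/2 = 0.25 × d6
- Three points: 0.25 × (0 + d3)/2 + 0.25 × (d3 + d6)/2 = 0.25 × d3 + 0.125 × d6
- Planned minus three-point: 0.125 × d6 − 0.25 × d3 = 0.25 × (d6/2 − d3)

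The planned gain does not contain d3. It is too low when d3 exceeds half of d6, exact when d3 = d6/2, and too high when d3 is smaller than that.

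**Numbers.** The size of 0.05 is assumed. The percentages depend only on the ratio of d3 to d6. The last column is the factor by which a positive ICER is multiplied, with the cost difference held fixed (three-point gain divided by planned gain).

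| Path | d3 | d6 | Planned | Three-point | Error in QALY gain | ICER factor |
|---|---|---|---|---|---|---|
| Reached by three months, held | 0.05 | 0.05 | 0.0125 | 0.0188 | 33% too low | 1.5 |
| Halved by six months | 0.05 | 0.025 | 0.0063 | 0.0156 | 60% too low | 2.5 |
| Lost by six months | 0.05 | 0 | 0 | 0.0125 | 100% too low | undefined |
| Somewhat front-loaded | 0.03 | 0.05 | 0.0125 | 0.0138 | 9% too low | 1.1 |
| Linear build-up | 0.025 | 0.05 | 0.0125 | 0.0125 | none | 1.0 |
| Somewhat late | 0.02 | 0.05 | 0.0125 | 0.0113 | 11% too high | 0.9 |
| Only after three months | 0 | 0.05 | 0.0125 | 0.0063 | 100% too high | 0.5 |

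The planned bootstrap interval around the ICER reflects sampling error. It resamples the same two-point QALYs and cannot reveal or correct this error.

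**The case against.** A reader might infer that the ICER is biased against occupational therapy. The documents do not support so firm a statement. The error has no fixed sign, and no utility path is given. The early effect that the protocol fixes is on COPM performance, not on EQ-5D. The Background puts quality of life downstream of improved daily functioning, so some lag is conceivable. The intervention also supports self-management, and a few participants wait for aids or adaptations, although the protocol calls those cases incidental. This objection stands: the gap in the schedule is certain, its direction is not.

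It can also be said that the consequence is limited. The primary outcome and the clinical analyses are untouched, and the second economic measure, cost per successful treatment based on a COPM gain of 2 points at six months, does not use EQ-5D. A two-point trapezium is a coarse but recognised approximation and contradicts nothing in the article. All of that is fair and limits the weight of the point.

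The omission cannot be put down to a journal article condensing a fuller plan. Table 1 positively fixes the schedule, and no analysis plan can restore a measurement that was not taken. The one budgetary reason given explains the telephone assessment at six months, not the missing EQ-5D at three.

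**Conclusion.** The point holds as a weakness of the cost-utility analysis with a conditional direction. The planned QALY gain ignores utility at three months. Against a three-point trapezium it is 33% to 100% too low if a full three-month gain is held, halves or disappears, exact under linear build-up, and up to twofold too high if there is no gain before three months. These figures assume no baseline difference and no harm at three months, and take the three-point trapezium as the reference, which is itself an approximation.

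Ten weeks of treatment, a three-month primary time point and no planned therapy afterwards make understatement of the QALY gain the more plausible direction, and with it an overstated ICER when the cost difference is positive. That is a judgement from the design, not something the protocol establishes. The cost-per-successful-treatment ratio is not affected.

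**What to change.** If the dash in Table 1 is a typing error, correct the table. Otherwise add EQ-5D for patients and caregivers to the existing three-month questionnaire set, and compute a three-point trapezium QALY wherever the three-month value is measured.

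The article reports the trial as ongoing, with recruitment expected to end by November 2012, so some participants may already be past that visit. For them, keep the two-point QALY and run a sensitivity analysis beside it with predicted three-month utilities: from PDQ-39 and VAS QoL for patients, and from VAS QoL, ZBI and HADS for caregivers. All of these are collected at all three times, so the two prediction models can be fitted at baseline and six months, where EQ-5D is also available. Carry the imputation uncertainty into the bootstrap. A modelled utility should not become the main QALY for these participants: the models would be fitted partly on the six-month telephone assessment and applied to the three-month assessment.

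The cost is one short questionnaire at a visit that already takes place, a small amendment, slight extra burden for participants, and some analysis work for the two models.

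### No baseline adjustment is stated for the QALY difference that enters the ICER, although half the weight of each two-point QALY is the pre-treatment EQ-5D score

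*Protocol article*

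**What the plan says.** The protocol article, under Analysis cost-effectiveness, takes the steps in this order.

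- Costs: "Differences in costs between groups over a six-month timeframe will be estimated using regression analysis taking into account potential co-variants".
- Effects: "utility will be calculated as quality adjusted life year (QALY) over a timeframe of six months using the trapezium rule". The source is given as follows: "QALYs for patients and caregivers are derived from the EuroQol EQ-5D scores using the EQ-5D health tariffs for the Dutch population".
- Combination: "Then, cost and QALY differences are combined in an incremental cost-effectiveness ratio (ICER".
- Uncertainty: "using the bootstrap method, confidence intervals surrounding this ICER will be estimated".

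Table 1 (Assessment procedures) marks EQ-5D at baseline and at six months, with a dash at three months. The minimization factors (Trial design) are COPM performance, Hoehn and Yahr score, gender, age group and physiotherapy. EQ-5D is not among them.

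For the clinical outcome, Analysis effectiveness is explicit: "The baseline COPM scores (T0) and the minimization factors will be covariates". It then extends the approach: "Similarly, a secondary analysis will be done evaluating the secondary outcome variables and outcomes for six months". QALYs are not named there.

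**The concern.** The section gives an estimator with covariates for the numerator of the ICER and none for the denominator. Followed as written, it leads to a covariate-adjusted cost difference divided by a plain difference in mean QALYs.

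A two-point QALY makes this matter more than it would for an ordinary follow-up score, because the baseline utility is itself a component of the outcome. Any chance difference between arms in baseline EQ-5D passes straight into the QALY difference, although it cannot be an effect of treatment. Cost-effectiveness is a stated aim of the trial, so the precision of the denominator is worth protecting. Fixing the estimator in advance also removes the choice of whether to adjust once the baseline imbalance has been seen.

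**Working it through.** **Inputs from the article.** EQ-5D is measured at 0 and 6 months, the QALY uses the trapezium rule over half a year, and the sample size section targets 56 control and 112 intervention patients. The article states no SD, correlation, standard error or power for EQ-5D, QALYs or the ICER, so there is no plan figure for this quantity to reproduce. The baseline-to-outcome correlation of about 0.5 in the sample size section is for COPM. The plan uses it as a baseline-adjustment gain: 75 × (1 − 0.5²) = 56.25 and 150 × 0.75 = 112.5, hence 56 and 112.

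**Inputs assumed.** r is the EQ-5D correlation between baseline and six months, shown over a range. s is the EQ-5D SD, taken as equal at both times. Allocation is treated as simple randomization.

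**Step 1, weight of baseline.** QALY = 0.5 × (u0 + u6)/2 = 0.25 × (u0 + u6). Each score has weight 0.25, so baseline has half the total.

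**Step 2, variance per patient.**
- Plain: 0.0625 × s² × (2 + 2r)
- Adjusted for u0: 0.0625 × s² × (1 − r²)
- Ratio of standard errors: √[2(1 + r)/((1 − r)(1 + r))] = √(2/(1 − r)), in which s cancels

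**Step 3, effect of imbalance.** Given an observed baseline difference D between arms, the plain QALY difference is shifted by 0.25 × D directly. Because u6 is correlated with u0, the expected total shift is 0.25 × (1 + r) × D. The adjusted difference removes this.

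| r (assumed) | Plain variance / s² | Adjusted variance / s² | SE ratio | Expected shift |
|---|---|---|---|---|
| 0 | 0.1250 | 0.0625 | 1.41 | 0.250 D |
| 0.3 | 0.1625 | 0.0569 | 1.69 | 0.325 D |
| 0.5 | 0.1875 | 0.0469 | 2.00 | 0.375 D |
| 0.7 | 0.2125 | 0.0319 | 2.58 | 0.425 D |

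A simulation of 8,000 trials with 56 versus 112 patients gave SE ratios of 1.68, 2.00 and 2.57 at r = 0.3, 0.5 and 0.7. The mean error of the plain difference was essentially zero (at most 0.0003 QALY in size).

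**Step 4, unequal SDs.** If the six-month SD is k times the baseline SD, the ratio is √[(1 + k² + 2rk)/(k²(1 − r²))]. At r = 0.5 this is 2.25 for k = 0.8 and 1.80 for k = 1.25.

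**Step 5, scale, for illustration only.** Take s = 0.2 (assumed) and r = 0.5. With √(1/56 + 1/112) = 0.1637:
- Plain SE: 0.25 × 0.2 × √3 × 0.1637 = 0.0142 QALY
- Adjusted SE: 0.25 × 0.2 × √0.75 × 0.1637 = 0.0071 QALY
- One standard error of baseline imbalance: 0.2 × 0.1637 = 0.0327, an expected shift of 0.375 × 0.0327 = 0.0123 QALY

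All of these scale in proportion to s.

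**Step 6, link to the clinical analysis.** Regress 0.25 × (u0 + u6) on arm, u0 and other covariates. The 0.25 × u0 part is absorbed by the u0 term, so the arm coefficient is exactly 0.25 times that from the ANCOVA of u6 on the same covariates in the same patients.

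**The case against.** The strongest reply is that silence is not a decision. A reader might infer that the plan has chosen an unadjusted QALY comparison. The article does not say so. It gives no estimator for the QALY difference, it leaves even the cost covariates unnamed, and it is a condensed account whose full protocol or analysis plan may supply the detail. This stands, and the point is limited to what the text states for costs and does not state for QALYs.

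Secondly, the article says that all secondary outcomes are listed in Table 1, and EQ-5D is listed there. Extending the covariance model to secondary and six-month outcomes therefore plausibly covers six-month EQ-5D. By step 6, the adjusted QALY difference is a rescaling of that analysis. This also stands, and it makes the remedy easy. But nothing carries that estimate into the ICER or its bootstrap. If EQ-5D is analysed by ANCOVA and QALYs by plain difference, the two could disagree, even in sign.

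Thirdly, minimization on COPM, disease stage, age, gender and physiotherapy will balance EQ-5D in part, as far as those factors correlate with it. To that extent the ratios above overstate the loss.

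Finally, a reader might infer bias or an invalid interval. Neither follows: under randomization the plain difference is unbiased on average, and a bootstrap of it reflects its wider spread.

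**Conclusion.** The point holds as an avoidable loss of precision, together with exposure to whatever baseline imbalance happens to occur. As written, the article adjusts the cost difference and states no baseline adjustment for the QALY difference, although half the weight of each QALY is pre-treatment. With equal SDs and r of at least 0, the standard error of the plain QALY difference is at least 1.41 times the adjusted one, and 1.69 to 2.58 times for r from 0.3 to 0.7, under simple randomization.

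It is tempting to say that the standard error is doubled, or that the uncertainty of the ICER is. The documents support neither. A factor of 2.00 needs an EQ-5D correlation of 0.5, and the article's 0.5 belongs to COPM. The factor applies to the QALY difference only, since the ICER is a ratio whose interval also depends on costs. This is an improvement worth making, not a flaw that invalidates the economic evaluation.

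**What to change.** State under Analysis cost-effectiveness, or in the analysis plan, that:

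- the QALY difference is estimated by regression on arm, baseline EQ-5D and the minimization factors, separately for patients and for caregivers, each with their own baseline EQ-5D;
- this regression and the cost regression are fitted together in each bootstrap replicate, so that the correlation between costs and effects is kept;
- the adjusted differences are the ones used in the ICER.

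The cost is a sentence or two of text and a short change to the analysis code. Baseline EQ-5D and the minimization factors are already scheduled for collection, and neither the visits nor the sample size changes. The result agrees with the covariance approach under Analysis effectiveness, being 0.25 times the six-month EQ-5D effect with the same covariates. If the full analysis plan already says this, a cross-reference is enough.

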Our hypothesis is that OT according to the Dutch guidelines has an *added* value within multidisciplinary care for patients with Parkinson’s disease and their caregivers. We expect that addressing the complex occupational performance issues from an OT perspective will improve daily functioning, more so than if OT is not involved. Improved daily functioning will result in enhanced participation in daily activities among patients, reduced caregiver burden, an improved quality of life for both patients and caregivers, and a reduction in costs for society. To test this hypothesis, we followed the steps of the framework for evaluation of complex interventions of the Medical Research Council [20,21]. Based on a phase II exploratory trial [22] we have improved the procedures for the currently proposed randomized controlled trial (phase III trial). This trial, the OTiP study, evaluates the effectiveness and cost-effectiveness of OT according to the Dutch guidelines for OT in Parkinson’s disease.

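### The planned bootstrap interval is on the ICER itself, which cannot be read in the better-and-cheaper quadrant that the trial hypothesises

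*Protocol article*

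**What the plan says.** Under 'Analysis cost-effectiveness' the protocol article forms an ICER from the differences in costs and QALYs and states that "using the bootstrap method, confidence intervals surrounding this ICER will be estimated". This is the only joint uncertainty measure named there. The same section says "utility will be calculated as quality adjusted life year (QALY) over a timeframe of six months using the trapezium rule", and adds a second ratio: "We also measure cost-effectiveness by costs per successful treatment". No interval is stated for that second ratio.

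The closing paragraph of the Background gives the expected direction: better daily functioning should lead to "an improved quality of life for both patients and caregivers, and a reduction in costs for society". Table 1 ('Assessment procedures') has the EQ-5D at baseline and six months but not at three months.

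**The concern.** A ratio of cost difference to QALY difference can be ranked only when there is a trade-off: more QALYs at more cost, or fewer QALYs at less cost. The trial hypothesises neither; it expects more QALYs at lower cost. There the ratio is negative, and its size says nothing consistent about how good the result is. The opposite result, higher cost with fewer QALYs, is negative too. The ratio also jumps between plus and minus infinity where the QALY difference passes zero.

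At stake is the joint summary of costs and QALYs, for a trial that has cost-effectiveness as a stated aim. If the hypothesis is right, the reported limits could not tell a reader how sure the trial is that therapy is worth its cost.

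**Working it through.** **1. Inputs.** From the article: interval on the ICER, six-month horizon, trapezium rule ('Analysis cost-effectiveness'); expected direction (Background); EQ-5D time points (Table 1); 56 control and 112 intervention patients ('Sample size calculation', taken as stated). The article gives no ICER, QALY difference, EQ-5D SD or cost SD, so there is no figure of its own to reproduce. All utility, cost and willingness-to-pay values below are assumptions.

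**2. The ratio in the hypothesised quadrant.** ICER = cost difference / QALY difference. Net benefit = 20,000 x QALY difference - cost difference, with 20,000 per QALY for illustration only.

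| Cost difference | QALY difference | ICER | Net benefit |
|---|---|---|---|
| -500 | +0.0125 | -40,000 | 250 + 500 = +750 |
| +500 | -0.0125 | -40,000 | -250 - 500 = -750 |
| -500 | +0.025 | -20,000 | 500 + 500 = +1,000 |
| -1,000 | +0.0125 | -80,000 | 250 + 1,000 = +1,250 |

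Rows 1 and 2 share one ICER and are opposite conclusions. Rows 3 and 4 are both better than row 1, yet one moves the ICER toward zero and the other away from it. The algebra holds for any values of these signs, so this part does not depend on the assumed figures.

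**3. Crossing a zero QALY difference.** With EQ-5D at 0 and 6 months, the trapezium rule gives QALY = 0.5 x (U0 + U6)/2 = 0.25(U0 + U6). With balanced baselines, a utility gain of 0.05 at six months is 0.25 x 0.05 = 0.0125 QALY. For utility SD s and baseline-to-follow-up correlation r:

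- Unadjusted SE = 0.25 s sqrt(2(1 + r)) x sqrt(1/56 + 1/112)
- Baseline-adjusted SE = 0.25 s sqrt(1 - r^2) x sqrt(1/56 + 1/112)
- Share of replicates below zero = Phi(-QALY difference / SE), taking the observed difference equal to the assumed one

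Here sqrt(1/56 + 1/112) = 0.1637. For s = 0.2 and r = 0.5:

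- Unadjusted: SE = 0.0866 x 0.1637 = 0.0142; Phi(-0.0125/0.0142) = 0.19
- Adjusted: SE = 0.0433 x 0.1637 = 0.0071; Phi(-0.0125/0.0071) = 0.04

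Over s = 0.15 to 0.30 and r = 0.5 to 0.7:

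| Utility gain | Below zero, unadjusted | Below zero, adjusted |
|---|---|---|
| 0.02 | 32-41% | 13-32% |
| 0.05 | 12-29% | 0.2-12% |
| 0.10 | 0.9-13.5% | below 1% |

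To keep the share below 2.5%, the gain must exceed 1.96 x SE / 0.25, which is about 0.08-0.18 unadjusted or 0.03-0.08 adjusted. With all 192 patients, the row for 0.05 becomes 10-28% and 0.1-10%.

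**4. Illustration.** One simulated data set of 168 patients, 5,000 replicates, assumed QALY SD 0.10, cost SD 6,000, QALY gain 0.02 and saving 500 (ICER -500/0.02 = -25,000). Replicates: 58% better and cheaper, 27% better and dearer, 11% worse and cheaper, 4% worse and dearer. The percentile limits of the ICER are about -511,000 and +476,000. Net benefit from the same replicates has limits of -1,082 and 2,816 at 20,000 per QALY (probability cost-effective 0.81), and of -1,320 and 5,370 at 80,000 (0.89).

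**The case against.** Several objections have force.

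- **A bootstrap ICER interval is not wrong in general.** It is acceptable when the replicates stay in one trade-off quadrant. That stands. The fault is specific to this trial, whose hypothesis places the result outside a trade-off quadrant.
- **The article does not say how the limits are formed.** Sorting replicates and taking percentiles is one way; joint regions on the plane are another. Construction and display are commonly left to the full protocol or analysis plan, so the absence of a plane or acceptability curve is not in itself a fault. What the article does fix is that the interval is on the ratio, and that is the point here.
- **Zero crossing is not certain.** A reader might infer that replicates are bound to fall on both sides of zero. The documents do not support this: they give no QALY variance, and with a large gain, or a moderate one with baseline adjustment, crossings can be negligible. Nor does the article say that it expects a small QALY difference; the values in the working are assumptions.
- **Uncertainty is not lost altogether.** A reader might infer that the economic question would have no valid statement of uncertainty. That goes too far: a regression estimate of the cost difference and analyses of the secondary outcomes are planned separately. Only the joint summary is affected.
- **Cost per successful treatment.** A reader might extend the fault to this ratio. The article states no interval for it, so the point applies only if one is reported.

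**Conclusion.** The point holds in a limited form. The article fixes a confidence interval on the ICER. Under its own hypothesis of better and cheaper, that ratio is negative, unordered in benefit, and indistinguishable from the ratio of a worse and dearer result. The interval therefore cannot be interpreted as a range from good to poor value. This rests only on the Background, the cost-effectiveness section and the algebra of the ratio.

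The crossing of zero is a possible further problem whose size rests on assumptions: roughly 12-29% of replicates unadjusted and 0.2-12% adjusted at a utility gain of 0.05, more for smaller gains and few for large ones.

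The change should be made because it is cheap and concerns a stated aim of the trial.

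**What to change.** In 'Analysis cost-effectiveness', keep the bootstrap of the joint cost and QALY differences and change what is reported from it:

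- Replace the ICER interval by incremental net monetary benefit (willingness-to-pay x QALY difference - cost difference) with a bootstrap 95% confidence interval over a prespecified range of willingness-to-pay values.
- Show the same replicates on the cost-effectiveness plane and as an acceptability curve.
- Give the ICER as a point estimate only when it lies in a trade-off quadrant; otherwise report 'dominant' or 'dominated'.
- If an interval is given for cost per successful treatment, handle it in the same way, with a range of values per additional success.

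The cost is wording and the need to name a willingness-to-pay range. No new data are needed, and the same replicates serve every display.
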